### 2.6. Statistical Analysis

CBS scores, those of personal neglect, mean egocentric errors and mental evocation, the time needed to finish the wheelchair course and the number of bumps in each direction will be entered as quantitative data.

After having verified the required assumptions about data distributions (Shapiro–Wilk test of normality, Levene’s test of homoscedasticity, Box’s M-test of covariance homogeneity and Mauchly’s test of sphericity), a mixed analysis of variance (with repeated measures for the SSA) will be performed on each quantitative variable with test periods (Pre, Postsession1, Postweek1, Postweek3, Postweek6) as within-subject factors and treatment groups (control, left-NMV, left-NMV + sham-tDCS, left-NMV + a-tDCS) as between-subject factors. Post hoc tests will be conducted using Tukey’s honestly significant difference method when needed, and *p*-values will be adjusted with the Bonferroni method. Size effects will be reported using the η2 (Eta-square) for each ANOVA and Cohen’s d for each Tukey’s post hoc test, along with confidence intervals.

If the conditions for using parametric tests are not met, then non-parametric statistical analyses of comparisons between test periods and groups will be performed. For each treatment group, we will perform a Friedman test to analyze the effect of the test period on each quantitative variable independently. When a Friedman test is significant, post hoc Wilcoxon signed rank tests with the Bonferroni adjustment method will be used to perform pairwise comparisons between each of the five time points. Kruskal–Wallis tests will be performed to compare the treatment groups. First, a Kruskal–Wallis test will be performed on the sum of ranks of the scores in each group before the first session in order to ensure that the initial mean scores (Pre) are equivalent between groups. Second, the effect of treatment will be calculated for each participant at each post-session assessment (Postsession1, Postweek1, Postweek3, Postweek6) by subtracting the mean initial score (Pre) from each quantitative data, independently. In order to analyze the effect of the treatment received on the evolution of quantitative data, Kruskal–Wallis tests will be performed on the sum of ranks of the Post–Pre score differences in each group. When the Kruskal–Wallis test is significant, post hoc pairwise comparisons between groups will be calculated, and the *p*-value will be adjusted by the Steel–Dwass–Critchlow–Fligner method.

Any participant with a missing score on any of the assessment sessions will be excluded from the statistical analysis for that specific test.

All statistical analyses will be performed using R software (version 2021.09.1 Build 372). The threshold for statistical significance will be set at α = 0.05.

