
USN rehabilitation remains a public health issue in terms of patients’ independence and healthcare costs. One of its main challenges lies in offering therapeutic innovations that can be easily integrated into conventional practice [34]. NMV and tDCS appear to be easy-to-use techniques that could meet this core condition for the rehabilitation of USN. The aim of the present protocol study is to assess beneficial effects on USN, specifically on immediate and long-term functional outcomes and neuropsychological aspects of spatial recovery, induced by a combined treatment associating the left-side NMV technique and a-tDCS on the i-PPC during occupational therapy sessions in patients with left USN. Our hypothesis is that the increase in excitability of the lesioned hemisphere induced by a-tDCS will amplify the lasting beneficial effects of left-side NMV during conventional occupational therapy sessions.

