## 2. Materials and Methods

This multicentric prospective randomized controlled superiority trial will focus on assessing the benefits of our therapeutic protocol on independence in daily life activities, neuropsychological aspects of different spatial components of USN (personal, extra-personal and representational neglect) and egocentric spatial perception assessments, using a mixed measurement design. The HEMISTIM protocol will take place in three neurological rehabilitation centers in Grand-Est and Provence-Alpes Côte d’Azur regions, France.

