#### 2.4.3. Setting of Assessments

In this study, the primary outcome will be the evolution of the global USN behavior evaluated by the Catherine Bergego Scale (CBS) [38], a functional scale assessing USN severity in daily life situations.

In addition, various USN spatial cognitive-motor skills will be assessed as secondary outcomes by the following five tests.

The Fluff test [39] aims at investigating personal neglect with targets attached to patients’ clothes, as illustrated in Figure 2a. The number of removed targets will be counted in order to calculate a score of personal neglect expressed as the difference of percentages of targets found on each side of the body (left–right), this value becoming more negative with the severity of personal neglect.

Gainotti’s drawing copying test [40], illustrated in Figure 2b, informs us on two kinds of peri-personal neglect referring to distinct disturbances of mental representations involved: space-centered neglect (egocentric) and object-centered neglect (allocentric). Therapists will verify throughout the test that the patient remains centered in relation to the paper. The quality of the drawing will be evaluated with respect to allocentric and egocentric reference frames.

The Map of France test [41] is designed to investigate representational neglect. The number of cities mentioned by the patient will be counted on either side of a median line drawn vertically through the center of France (Lille–Perpignan axis; see Figure 2c). A mental evocation score will be calculated as the ratio of the number of cities on each side of this axis (left/right). In addition, the strategy and order of mention will be recorded for qualitative analysis.

The Subjective Straight-Ahead test (SSA) [21] investigates the accuracy of egocentric perception, using the experimental device pictured in Figure 2d. The centered position of the patient will be verified throughout the test. Egocentric perception will be expressed as the mean error of 20 successive trials, after measuring for each trial the angular difference between the measured angles of the hand pointed toward the SSA direction and the objective straight-ahead direction of the patient’s body. A higher score indicates a less accurate egocentric perception; leftward errors will be assigned as negative values and rightward errors as positive values.

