### 2.5. Sample Size Calculation

To determine the number of left USN patients to include, we sought to perform an a priori headcount calculation based on published work in the field. However, none of them have combined NMV and tDCS or used the CBS score as the primary endpoint. No a priori power calculation could therefore be performed, but we were inspired by the number of patients included in the works of Làdavas et al. [32] and Turgut et al. [33], both of whom used tDCS on USN patients, the former combined with visual prisms and the latter with optokinetic drift. These two studies included 30 and 32 patients, respectively, which were divided for the first in two groups of 11 patients and one group of 8, and for the second in two groups of 16 patients. Thus, we estimated that 48 patients would be necessary for our study, randomly and homogeneously distributed in each of the 4 groups. To ensure that the target number of patients is recruited, three neurological rehabilitation centers admitting each year a large number of patients meeting the inclusion criteria will be involved. We will verify a posteriori that the groups do not differ in sex, mean age, education, duration of illness, or baseline CBS scores, and that they have similar stroke locations.

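### The primary CBS analysis is a four-group by five-period ANOVA with no decisive term, group pair or time point, so a significant result need not concern tDCS

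*Protocol article*

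**What the plan says.** The Introduction states the hypothesis that the "increase in excitability of the lesioned hemisphere induced by a-tDCS will amplify the lasting beneficial effects of left-side NMV". Section 2 presents the study in these words: "This multicentric prospective randomized controlled superiority trial". Section 2.4.3 says that "the primary outcome will be the evolution of the global USN behavior evaluated by the Catherine Bergego Scale", without giving a time point.

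Section 2.6 applies one model to the CBS and to every other quantitative variable: "a mixed analysis of variance (with repeated measures for the SSA) will be performed on each quantitative variable with test periods". The periods are "Pre, Postsession1, Postweek1, Postweek3, Postweek6) as within-subject factors", and the four arms are the between-subject factor. Tukey comparisons follow only where needed, and Bonferroni adjustment of p-values is also mentioned. If the parametric assumptions fail, Kruskal–Wallis tests on Post–Pre differences across the four groups take over, with pairwise tests only after a significant result.

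Section 2.5 reports that no power calculation could be made and takes the number from two earlier tDCS studies: "Thus, we estimated that 48 patients would be necessary for our study".

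**The concern.** The hypothesis concerns what anodal tDCS adds to NMV. Only the active and sham tDCS arms differ in that respect alone. The plan does not make their comparison the primary test. It runs an undirected test over all arms and periods and leaves open which result counts as success: the group term, the period term, the interaction, or any of the pairs.

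A superiority trial analysed this way could report a significant primary analysis that reflects only NMV against no NMV. If the period term were read as the result, it could reflect only recovery shared by all arms. With no rule set in advance, a reader could not tell a confirmed hypothesis from a comparison picked after the data were seen.

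**Working it through.** **Inputs from the protocol article.** Four groups and five periods (2.6); 48 patients shared equally (2.5), so 48/4 = 12 per group; α = 0.05 (2.6; two-sided is assumed). No effect size, SD, correlation or power is given.

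**The plan's own figure.** Without those inputs, no formula can reproduce 48. Scaling the cited group sizes of 8, 11 and 16 to four groups gives 32, 44 and 64, so 48 lies within that range but is not derived from it.

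**Number of candidate tests.** Group pairs: 4 × 3/2 = 6. With four follow-ups: 6 × 4 = 24. The interaction has (4 − 1)(5 − 1) = 12 df, with (48 − 4)(5 − 1) = 176 error df.

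**Assumptions for illustration.** Compound symmetry; correlation 0.5 or 0.7; effects in SDs of a single CBS score; two effect profiles over the five periods, (0, 0.25, 0.5, 1, 1) and (0, 0, 1/3, 1, 1), as shares of the full difference.

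**(a) No tDCS effect; control differs equally from the three NMV arms.** Simulated share of trials with a significant interaction, ranging over the two profiles:

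| Difference | Correlation 0.5 | Correlation 0.7 |
|---|---|---|
| 0.5 SD | 17–22% | 28–36% |
| 0.8 SD | 44–56% | 70–83% |
| 1.0 SD | 66–80% | 91–97% |

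In the same trials, a single contrast of a-tDCS against sham is significant in 5%, as it should be.

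**(b) Only a-tDCS differs.** Power to find a-tDCS against sham on change from Pre, with the first profile:

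| Difference | Tukey pair, corr. 0.5 | One contrast, corr. 0.5 | Tukey pair, corr. 0.7 | One contrast, corr. 0.7 |
|---|---|---|---|---|
| 0.5 SD | 9% | 22% | 15% | 34% |
| 0.8 SD | 25% | 49% | 45% | 70% |
| 1.0 SD | 42% | 67% | 69% | 87% |

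Requiring a significant interaction first lowers the Tukey route at 1.0 SD to about 37–40% (correlation 0.5) or 67–68% (0.7). One contrast adjusted for baseline CBS reaches about 78% or 91%.

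**(c) Detectable difference with 12 per arm.** For one contrast the noncentrality is d√(12/2) = 2.449d, with 44 df. Power is 80% at d ≈ 1.17 for one unadjusted contrast at two-sided 0.05, and at d ≈ 1.44 for a Tukey pair. Here d is in SDs of the analysed score.

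**The case against.** The strongest reply is that the Tukey step covers all six pairs, with effect sizes and confidence intervals, so a difference due to control would be seen for what it is. That is largely fair. A reader might infer that the plan would wrongly credit tDCS, but with no tDCS effect the Tukey pair of a-tDCS against sham is significant in only about 1% of the simulated trials. What stands is that nothing makes that pair decisive.

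Other stronger readings do not hold either:

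- **That the omnibus test is weak.** It is not consistently weaker than the single contrast: 44% against 49% at 0.8 SD and correlation 0.5, but 91% against 87% at 1.0 SD and 0.7. Its fault is that it does not identify tDCS. Low power comes mainly from 12 per arm, and Section 2.5 admits that this was not based on power.
- **That Tukey p-values are multiplied again by six.** Section 2.6 mentions Bonferroni but gives neither a family nor a multiplier. Adding it would lower power further, but by how much cannot be read from the text.
- **That the planned comparison ignores baseline.** The outcome is evolution, the fallback uses Post–Pre differences, and the Discussion speaks of change from baseline. Change from Pre is the fair basis.
- **That rating the CBS just after the first session spoils the test.** The documents do not show this, and the power of the interaction with that period included speaks against it.
- **That the trial has only one question.** The aims include immediate effects, and the Discussion expects NMV itself to help, so NMV against control answers a stated expectation, though not the tDCS hypothesis.

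Nor is this detail that an article leaves to another document: Section 2.6 sets out assumption tests, model, post hoc methods and fallback. The objection is to what it fixes.

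**Conclusion.** The point holds. The stated primary analysis does not identify the comparison that carries the hypothesis, and a significant interaction can arise with no tDCS effect. How often ranges from about one trial in six (0.5 SD, correlation 0.5) to nearly all (1.0 SD, correlation 0.7). On the same change-from-Pre scale, with a true a-tDCS difference of 1.0 SD, naming the contrast gains roughly 27–30 points of power at correlation 0.5 and about 20 at 0.7; adjusting for baseline adds some more.

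Every percentage rests on assumed effects, correlations and time profiles and on 12 complete patients per arm. The structural defect does not depend on them. The fallback has the same structure. Naming the contrast does not cure the small sample: at 0.8 SD of the analysed score, one unadjusted contrast still has only about 48% power.

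**What to change.** In Section 2.6, before unblinding, name one primary test: the difference in CBS between left-NMV + a-tDCS and left-NMV + sham-tDCS at one late time point, adjusted for baseline CBS, at two-sided α = 0.05. The sponsor should choose Postweek3 or Postweek6 in advance; the documents rank neither, and either choice resolves the point. Report the omnibus ANOVA, the other pairs and the other periods as secondary results with confidence intervals. Make the same contrast primary under the non-parametric fallback.

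In Section 2.5, replace the statement that 48 patients are necessary by the difference that 12 per arm can detect with 80% power on this contrast: about 1.2 SD unadjusted, less with baseline adjustment.

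The cost is wording only, with no added patients, visits or measurements. The one small downside is that NMV against control and the remaining pairs become secondary.

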#### 2.4.1. Inclusion in Groups

The first week will allow us to include patients with left USN and to randomly assign them to four independent parallel groups (centralized randomization in a 1:1 ratio performed using a custom made algorithm on Matlab (MathWorks, Inc., Natick, MA, USA) by a blinded investigator: a control group receiving no additional treatment to conventional occupational therapy sessions and three experimental groups receiving in addition to the usual treatment either left-NMV, left-NMV + sham-tDCS or left-NMV + a-tDCS experimental treatments, administered by trained occupational therapists.

In these three experimental groups, each patient will be equipped with vibratory stimulators during conventional occupational therapy sessions taking place on Monday, Wednesday and Friday for three weeks from the second week on. The left-side NMV vibrator will be activated during the first 15 min of the occupational therapy session (lasting 45 min), as previously described [21,35]. In the two experimental groups receiving sham or a-tDCS, electrodes will be placed as described above. A continuous 2 mA current will be delivered for 20 min in the left-NMV + a-tDCS group, 5 min before (patients will be seated in a quiet room) and during the first 15 min of the occupational therapy session, simultaneously to the NMV stimulation. The current will be automatically turned off after 20 s in the left-NMV + sham-tDCS group, allowing the reproduction of the initial mild itching sensation at the beginning of active tDCS, thus ensuring that the patient stays blind to the activation status of the device. In the case of adverse events or unintended effects of trial interventions, the investigator who enrolled the patient will report its occurrence to the trial sponsor through a report form provided in the case report form.

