The Wheelchair navigation test [21], illustrated in Figure 3, aims at investigating spatial navigation skills and extra-personal neglect. The ride will be carried out once in each direction (A-B and B-A) to balance the number of obstacles and turns to the left and right. The time taken to finish the course will be measured and the number of bumps counted. Navigation quality will also be observed qualitatively (obstacle avoidance, goal strategy, perseverations).

Each test will be carried out several times over the study by a trained occupational therapist:

Baseline assessment (Pre): During the first week, each test (except for the CBS realized only once) will be repeated three times in order to obtain a reliable estimation of the participants’ performance level (mean values) before starting the experimental interventions.

Follow-up assessments: These will take place just at the end of the first experimental session (Postsession1), after the first and third weeks of the protocol (Postweek1 and Postweek3, respectively) and there will be a final evaluation three weeks after its ending (Postweek6). In addition, all patients will be asked about their expectations and satisfaction regarding the treatment at the end of each week of intervention.

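### The analysis of each quantitative outcome, including the primary CBS, is chosen by assumption tests on the trial data, with an undefined trigger and a fallback that does not hold the stated 0.05

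*Protocol article*

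**What the plan says.** Section 2.6 of the protocol article plans a mixed ANOVA for each quantitative variable, with five test periods within patients and four treatment groups between patients. It is to be run "After having verified the required assumptions about data distributions", and four tests are listed: Shapiro-Wilk, Levene, Box's M and Mauchly. The same section continues: "If the conditions for using parametric tests are not met, then non-parametric statistical analyses of comparisons between test periods and groups will be performed".

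The fallback has three parts:

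- a Friedman test over the periods, separately within each group;
- a Kruskal-Wallis test between groups at baseline;
- Kruskal-Wallis tests between groups on the change from Pre at each of the four later assessments. When such a test is significant, pairwise comparisons follow with Steel-Dwass-Critchlow-Fligner adjustment.

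The section closes with "The threshold for statistical significance will be set at α = 0.05". Section 2.5 fixes the size: "we estimated that 48 patients would be necessary for our study, randomly and homogeneously distributed in each of the 4 groups". Section 2.4.3 names the CBS as primary outcome and adds that at baseline every other test "will be repeated three times in order to obtain a reliable estimation", while the CBS is done once.

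**The concern.** A rule that picks the test from the data under analysis has three drawbacks here.

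- The gate consists of significance tests. At 12 per group they reject by chance when nothing is wrong, and they cannot show that the assumptions hold when they do not reject.
- Mauchly's test is an unsuitable gate. Departure from sphericity does not make the ANOVA unusable; it calls for corrected degrees of freedom or a model that leaves the covariance free. The stated rule allows it to lead to rank tests instead.
- The branches differ in error control. The ANOVA gives one omnibus test of group by period. The fallback gives four change-score tests, and no adjustment across those time points is stated.

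At stake is the primary comparison. Its method would be settled after the data are seen, could differ from one outcome to the next, and would not carry the 5% error rate that the article states.

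**Working it through.** **Inputs.** 48 patients in 4 equal groups (Sections 2.5 and 2.4.1), so 48/4 = 12 per group. Five periods and α = 0.05 (Section 2.6). There is no power calculation to reproduce; Section 2.5 states that none was done. The within-patient covariance of the CBS is not given, so a range is assumed, with normal data throughout.

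**Assumed reading.** Any one failed test triggers the switch. The article does not say so.

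**Step 1: chance failure of the gate.** For k independent tests at 5%, the chance of at least one rejection is 1 − 0.95^k.

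- Four single tests: 1 − 0.95^4 = 18.5%.
- Shapiro-Wilk on residuals in 5 periods, Levene in 5 periods, Box's M and Mauchly: k = 12, giving 1 − 0.95^12 = 46%.
- Shapiro-Wilk in 4 × 5 = 20 cells, with the rest as before: k = 27, giving 1 − 0.95^27 = 75%.

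The tests are correlated, so simulation is needed. With normal, homogeneous, spherical data the gate fails in 39 to 47% (residual-based Shapiro-Wilk) or 70 to 74% (per cell). Most of the spread within each range comes from centring Levene's test on the median or the mean.

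**Step 2: Mauchly's test alone.** Rejection at 48 patients is 5% under compound symmetry, 10% for a mainly random-intercept mixture, 30% with random slopes, 58 to 62% for serial correlation mixed with noise, 41% and 90% for AR(1) with correlation 0.3 and 0.5, and 99 to 100% for AR(1) with 0.7 to 0.9. For the secondary tests the baseline is a mean of three against single follow-ups. With assumed error variances of 0.1 and 0.3, that alone gives 46%. It does not apply to the CBS.

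**Step 3: the fallback.** Four Kruskal-Wallis tests of change, each at 5%, would give at least one false positive in 1 − 0.95^4 = 18.5% of trials if independent. Simulated with their actual correlation, the figure is 12 to 16%.

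**Step 4: the two-stage procedure.** With no treatment effect, run the gate. If it passes, test the uncorrected ANOVA interaction at 5%. If it fails, run the four Kruskal-Wallis tests and count any p < 0.05 as a finding. The table gives percentages from 2,000 trials per row (Mauchly column: 3,000). Ranges cover both Levene versions and, in the two-stage column, both Shapiro-Wilk readings.

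| Assumed covariance | Mauchly rejects | Gate fails, residuals | Gate fails, cells | Two-stage false positives | ANOVA interaction with Greenhouse-Geisser, no switch |
|---|---|---|---|---|---|
| Compound symmetry 0.7 | 5 | 39–46 | 70–73 | 9–13 | 4 |
| AR(1) 0.3 | 41 | 61–67 | 81–83 | 12–14 | 5 |
| AR(1) 0.5 | 90 | 92–93 | 96–97 | 13–14 | 4 |
| AR(1) 0.8 | 100 | 100 | 100 | 13 | 5 |

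Over all simulations run, the two-stage rate is about 9 to 15%. The excess comes mainly from the unadjusted fallback. The uncorrected ANOVA interaction alone reaches 8 to 11% under strong serial correlation, but there the gate nearly always fails, so that branch is seldom used.

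**Step 5: power.** One group is given an assumed extra change of 0.1, 0.4, 1 and 1 SD at the four follow-ups. Figures are for compound symmetry 0.7, AR(1) 0.8 and a mixed structure.

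- Greenhouse-Geisser interaction test: 95%, 73%, 81%.
- Any of four unadjusted Kruskal-Wallis tests: 95%, 72%, 85%.
- The same with Bonferroni over the four time points: 82%, 44%, 64%.

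The unadjusted fallback therefore matches the corrected ANOVA only by running at 12 to 16% error.

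**The case against.** The strongest reply is that the article condenses a fuller plan. The exact trigger and a sphericity correction are details commonly left to that plan, and their absence is no fault. That stands as far as absence goes. The point rests on what the article does state: a switch of method decided by tests on the outcome data, with sphericity among the conditions.

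Several stronger readings are tempting, and the document does not support them.

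- A reader might infer that sphericity will usually fail and that the ANOVA will mostly be replaced. Mauchly's rejection rate runs from about 5% to nearly 100% depending on a covariance the article does not give, and the switching rates need the any-failure reading. With ideal data and residual-based normality tests, the ANOVA would survive in more than half of trials.
- A reader might infer that the fallback contains no group-by-period test. It does: comparing groups on change from Pre is that contrast for one follow-up, and Section 2.6 gives it that purpose. What is missing is a single omnibus test and an adjustment across the four follow-ups.
- A reader might infer that some assessments are only minutes apart. Pre falls in the first week and sessions start in the second, so the periods are at least days apart.
- The mean-of-three baseline might be held against the primary outcome. The CBS is expressly exempt.

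It is also fair to object to one Gaussian model for everything. Bump counts and the left/right city ratio do not suit it, and the fix allows for that.

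**Conclusion.** The point holds in a limited form. The article fixes a data-driven choice of method for every quantitative outcome, leaves the trigger undefined, and lets non-sphericity lead to rank tests where a correction would do. If any failed test triggers the switch, the gate discards a valid ANOVA in about 40 to 47% of trials with ideal data (70 to 74% with per-cell normality tests), and more often under serial correlation. The two-stage false-positive rate is then about 9 to 15%, not 5%.

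These figures assume 12 per group, normal data, the any-failure trigger, and that a significant result at any follow-up counts as a finding, since Section 2.6 singles out none of the four. A stricter trigger would lower the switching rate, but the four fallback tests would still be unadjusted whenever they were used. The flaw is worth correcting before any outcome data are examined; it does not call the design into question.

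**What to change.** Delete the conditional switch in Section 2.6.

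- For the CBS and the other approximately continuous outcomes, pre-specify one analysis whatever the assumption tests show: a linear mixed model with unstructured covariance and Kenward-Roger degrees of freedom, or the planned mixed ANOVA with Greenhouse-Geisser correction. Name the group-by-period test as the single omnibus test.
- Always report a rank or permutation analysis of change from Pre as a sensitivity analysis, adjusted across the four follow-ups.
- Keep the assumption checks as diagnostics only.
- For bump counts and the left/right city ratio, name a count or rank-based method in advance.

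The cost is wording and slightly more analysis code. No extra patients or assessments are needed.

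### The a-tDCS versus sham contrast has no guaranteed estimate: the non-parametric branch gates pairwise comparisons on a significant omnibus test, and the ANOVA branch seems to

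*Protocol article*

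**What the plan says.** All of this is in the protocol article.

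- **Non-parametric branch (section 2.6).** Arms are compared by Kruskal–Wallis on the change from Pre at Postsession1, Postweek1, Postweek3 and Postweek6. Then: "When the Kruskal–Wallis test is significant, post hoc pairwise comparisons between groups will be calculated", with Steel–Dwass–Critchlow–Fligner adjustment. No effect size or interval is named for this branch.
- **Parametric branch (section 2.6).** After the mixed ANOVA, "Post hoc tests will be conducted using Tukey’s honestly significant difference method when needed". Effect sizes are η2 for each ANOVA, with no significance condition, and "Cohen’s d for each Tukey’s post hoc test, along with confidence intervals".
- **Hypothesis (section 1, last paragraph).** Anodal tDCS is expected to strengthen the lasting benefit of left-NMV. With a sham arm in the design, the direct test is left-NMV + a-tDCS against left-NMV + sham-tDCS.
- **Size (section 2.5).** "Thus, we estimated that 48 patients would be necessary for our study, randomly and homogeneously distributed in each of the 4 groups". The number follows the size of two cited studies, and "No a priori power calculation could therefore be performed".
- **Error rate (section 2.6).** "The threshold for statistical significance will be set at α = 0.05".

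**The concern.** A trial with 12 patients per arm and no power calculation is most useful for an unselected estimate of its key contrast, with an interval. Under the fallback rule as written, a non-significant Kruskal–Wallis test ends the between-arm analysis, and a-tDCS versus sham gets neither a comparison nor an estimate. A significant test leads to adjusted p-values, still with no named estimate. If the ANOVA branch is run the same way, Cohen's d for the contrast appears only in trials whose omnibus test succeeded. Those trials over-represent large observed differences, so the reported value overstates a real effect. η2 does not fill the gap, because it describes all four arms together and gives neither the direction nor the size of a-tDCS versus sham.

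The gate is also not needed to protect the error rate. Tukey's method and Steel–Dwass–Critchlow–Fligner each control the family-wise error over the pairwise comparisons without a preceding omnibus test.

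**Working it through.** **Inputs from the article.** N = 48 in four arms, "centralized randomization in a 1:1 ratio", so 48/4 = 12 per arm; α = 0.05. The 48 cannot be reproduced from a formula, because no effect size, SD or power is given. The cited group sizes ("divided for the first in two groups of 11 patients and one group of 8, and for the second in two groups of 16 patients") average (11 + 11 + 8 + 16 + 16)/5 = 12.4, which is close to 12.

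**Assumptions.** Normal change scores with SD 1; no dropout (a best case, since section 2.6 excludes patients with any missing score on a test); true a-tDCS minus sham difference d from 0.3 to 1.2 SD, positive meaning benefit. Two scenarios: (A) only the a-tDCS arm differs, with means 0, 0, 0, d; (B) NMV also works, with means 0, 0.5, 0.5, 0.5 + d.

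**Chance that the gate opens at one assessment.** For the one-way F test, noncentrality λ = 12 × Σ(μ_j − μ̄)², with 3 and 44 degrees of freedom and critical value 2.816.

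- A, d = 0.5: μ̄ = 0.125; λ = 12 × (3 × 0.0156 + 0.1406) = 2.25; power 19.7%.
- B, d = 0.5: μ̄ = 0.5; λ = 12 × (0.25 + 0 + 0 + 0.25) = 6.0; power 47.9%.

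Kruskal–Wallis was simulated (at least 20,000 trials per row, chi-square with 3 df). The last column of each block is the mean a-tDCS minus sham difference, in SD, among trials with a significant Kruskal–Wallis test.

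| True d | A: F | A: K–W | A: mean if significant | B: F | B: K–W | B: mean if significant |
|---|---|---|---|---|---|---|
| 0.3 | 9.7% | 9% | 0.68 | 32.7% | 30% | 0.44 |
| 0.5 | 19.7% | 18% | 0.88 | 47.9% | 44% | 0.66 |
| 0.8 | 46.2% | 42% | 1.06 | 73.8% | 70% | 0.91 |
| 1.0 | 66.8% | 62% | 1.18 | 87.2% | 84% | 1.07 |
| 1.2 | 83.5% | 80% | 1.30 | 95.0% | 93% | 1.23 |

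Over all trials, without the gate, the mean difference returns the true value. At d = 0.5 the gated mean is 0.88/0.5 = 1.76 times the truth in A and 0.66/0.5 = 1.32 times in B. In A, the F gate reaches 50% at d of about 0.84.

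**Group-by-time gate in the mixed ANOVA.** Scenario A, five time points, within-patient correlation 0.5 or 0.7: it opens in about 18% of trials at d = 0.5 and 44% at d = 0.8. A true 0.5 then averages about 0.77.

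**Four post-baseline Kruskal–Wallis tests.** With the same effect at each period and change scores correlated 0.5 to 0.7, at least one gate opens at d = 0.5 in about 38–44% of trials in A and 70–78% in B; at d = 0.8, in about 69–75% and 91–94%. Estimates then exist only at the significant visits. In A at d = 0.5 these still average about 0.87 to 0.88.

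**Cost of the gate in tests.** In A, the chance of any Tukey finding falls from 19.7% to 17.8% at d = 0.5 and from 46.5% to 43.9% at d = 0.8.

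**Without the gate.** The standard error of the contrast is √(2/12) = 0.408 SD, so an unadjusted 95% CI is about ±1.96 × 0.408 = ±0.80 SD. Two-sided power of this single contrast is Φ(d/0.408 − 1.96): 23% at d = 0.5, 50% at 0.8 and 69% at 1.0. Power of 80% needs d = (1.960 + 0.842) × 0.408 = 1.14.

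**The case against.** Much of the opposing case stands, and it sets the limits of the point.

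- **The two branches differ.** The gate is explicit only in the fallback, and Cohen's d is planned only in the ANOVA branch. A reader might infer that every effect size in the plan depends on a significant omnibus test. The text does not say so: the ANOVA wording is open, and η2 is unconditional. It is fair to say only that this wording suggests a gate, in line with the explicit conditions on the Friedman and Kruskal–Wallis tests.
- **The fallback has no planned effect size to inflate.** The Kruskal–Wallis means above show what selection does to any difference presented beside a gated comparison. They do not describe an output that the article promises.
- **A reader might infer that the estimate will usually be missing.** The article gives no effect size, so this cannot be claimed. At one assessment it is true below about 0.84 SD (F test) if only a-tDCS differs. If NMV also adds 0.5 SD, which is nearer the authors' own expectation, it is true only up to about 0.5 SD. It is false at 1.0 SD or more, and four assessments raise the chance that something is reported.
- **An omnibus test followed by post hoc tests is conventional**, and the gate costs only about 2 to 3 percentage points in Tukey findings. Agreed: the harm is to estimation, not to error control.
- **A full analysis plan may list unconditional estimates.** It may, and silence on tables would be no finding. But the article fixes the condition itself, so a plan that follows it inherits the problem.

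**Conclusion.** The point holds in a limited form. The fallback explicitly withholds between-arm comparisons unless Kruskal–Wallis is significant, and it names no estimate even then. The ANOVA branch can be read the same way. As written, nothing guarantees an estimate of a-tDCS versus sham, and any estimate shown only after omnibus significance is biased upward in every scenario examined with a true a-tDCS effect. The bias runs from slight at 1.2 SD (1.23 to 1.30) to more than double at 0.3 SD when only a-tDCS differs (0.68). These sizes rest on assumed effects, normal change scores and a full 12 per arm. The existence of the gate does not rest on them.

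**What to change.** In section 2.6, remove the significance condition for the between-group comparisons of the CBS. State that between-arm differences in change from Pre, in particular left-NMV + a-tDCS versus left-NMV + sham-tDCS, will be reported in CBS points with 95% CIs at each period, whatever the omnibus result. Use the model-based mean difference in the parametric branch and the Hodges–Lehmann shift in the fallback. Keep Tukey or Steel–Dwass–Critchlow–Fligner for the adjusted p-values.

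The cost is about two sentences and a few more table rows, with no new data and no design change. The change removes selective reporting but does not cure low power: the interval will be wide, and the report should say so.
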